## 2.3 - Carboplatin

Cisplatin and carboplatin are highly effective anti-cancer drugs that have been used to treat a wide variety of malignancies[[12](#_ENREF_12)]. The formation of platinum adducts with nucleophilic sites in DNA molecules causes cell cycle arrest in G_1_ and G_0_[[13](#_ENREF_13)], and the activation of apoptotic pathways[[14](#_ENREF_14)]. This can interfere with the repair of radiation-induced damage and may explain the interaction between platinated drugs (cisplatin and carboplatin) and ionizing radiation[[15-17](#_ENREF_15)]. Pre-clinical studies have shown that gliomas are sensitive to these agents. Phase II studies of intravenous carboplatin, administered as single agent or in combination with other therapeutics, however, have shown only a modest impact on outcome[[12](#_ENREF_12)]. Median progression-free and overall survival was approximately 3 and 9 months, respectively.

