## 5.12 - Dosage escalation plan

The starting dose of carboplatin will be 2 µg. The carboplatin dose will be escalated in cohorts of 3 (maximum of 6 patients in each dose level if DLT occurs). Three patients will be entered first at Dose Level 1. In the absence of DLT, 3 more patients will be entered at the next higher dose level. If 1of 3 patients had DLT, an additional 3 patients will be entered at that dose level. Dose escalation will continue until DLT occurs in at least 2 out of 6 patients. The MTD will be defined as the highest dose level at which at least 5/6 patients could be treated without DLT. If 2 of 3 patients in Dose Level 1 demonstrate DLT, the next cohort of patients will receive Dose Level 0. At least 28 days must elapse between completing enrollment in a cohort level and beginning treatment at the next cohort level.

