## 5.13 - Dose-Limiting Toxicity (DLT)

DLTs are defined, in the presence of supportive care, as any Grade 3 or 4 toxicity that is possibly, probably, or definitely related to the study drug. The maximum tolerated dosage is defined as the dose level below that causing DLT in at least two patients. The length of the DLT window will be at least 28 days, and this time interval must elapse before completion of one cohort and initiation of the next.

Non-hematologic toxicities such as rash, nausea, vomiting and hypertension will only be considered DLTs if they remain grade 3 or greater despite maximal medical therapy 72 hours after maximal medical therapy is initiated. The first deep venous thrombosis or pulmonary embolism will not be considered a DLT because these complications are common among patients with high-grade gliomas. Patients who develop DVT and/or PE may receive anticoagulation therapy and resume the clinical trial once clinically stable. A second DVT or PE on optimal medical therapy will be considered a DLT.

| **Number of Patients with DLT**  **At a Given Dose Level** | **Escalation Decision Rule** |
| --- | --- |
| 0 out of 3 | Enter 3 patients at the next dose level |
| > 2 | Dose escalation will be stopped. This dose level will be declared the maximally administered dose (highest dose administered). Three (3) additional patients will be entered at the next lowest dose level if only 3 patients were treated previously at that dose. |
| 1 out of 3 | Enter at least 3 more patients at this dose level.   - If 0 of these 3 patients experience DLT, proceed to the next dose level. - If 1 or more of this group suffer DLT, then dose escalation is stopped, and this dose is declared the maximally administered dose. Three (3) additional patients will be entered at the next lowest dose level if only 3 patients were treated previously at that dose. |
| <1 out of 6 at highest dose level below the maximally administered dose | This is generally the recommended phase 2 dose. At least 6 patients must be entered at the recommended phase 2 dose. |

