# 9 - Statistical Considerations

A standard phase I study design utilizing dose escalation as defined in section 2.0 will be used. A maximum of 42 patients will be accrued. Descriptive statistics of response/efficacy and tolerance of treatments will be used. Only patients who received study drug will be considered for endpoint analysis. Patients that did not receive study treatment (catheter placement and convection enhance delivery of carboplatin) will be replaced at the current dose cohort.

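### The replacement rule in Section 9 lets a fully infused patient who leaves before day 28 without a recorded DLT fill one of the 3 or 6 escalation places

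*Protocol*

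**What the plan says.** Section 9 (Statistical Considerations) fixes two rules. On the analysis set: "Only patients who received study drug will be considered for endpoint analysis". On replacement: "Patients that did not receive study treatment (catheter placement and convection enhance delivery of carboplatin) will be replaced at the current dose cohort". Neither asks for any length of observation after the infusion.

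Section 5.13 defines a DLT as "any Grade 3 or 4 toxicity that is possibly, probably, or definitely related to the study drug", with some exceptions, and says of the window: "The length of the DLT window will be at least 28 days, and this time interval must elapse before completion of one cohort". Section 5.12 puts the interval slightly differently: "At least 28 days must elapse between completing enrollment in a cohort level and beginning treatment at the next cohort level". Both describe time that must pass between cohorts.

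The decision table in Section 5.13 works on the number of patients with a DLT. After none in three, the instruction is "Enter 3 patients at the next dose level". After one in three, three more are entered, and escalation goes on if none of those has a DLT. The size requirements at the MTD refer to patients entered or treated. The word evaluable, or an equivalent, does not appear.

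**The concern.** Consider a patient who receives the whole 72-hour infusion and, on day 7, dies of tumour progression, withdraws from follow-up or is lost. If no related Grade 3 or 4 event has been recorded, there is no DLT. The patient received study drug, so Section 9 keeps the patient in the analysis and gives no ground for replacement. The patient then stands as one of the 3, or one of the 6, without DLT, although three quarters of the 28-day window was never observed.

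Two nearby remedies would not help. A minimum-infusion requirement is met, because the patient was fully dosed. A longer or clearer gap between cohorts only adds calendar time and does not recover the missing observation.

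Each decision rests on 3 or 6 patients, so one unobserved patient is a large share of the evidence. The MTD is the primary result and may be carried into later studies (Section 1.1).

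**Working it through.** **The plan's own figures.** The protocol gives no early-loss rate and no operating characteristics, so there is no figure on this point to reproduce. Its one sample-size figure is the maximum of 42. That equals 7 levels × 6 patients, whereas the nine escalating levels in Section 5.12.1 could need 9 × 6 = 54. The point here does not depend on 42, but any replacement patients draw on the same cap.

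**Inputs from the protocol.** Escalate after 0 DLTs in 3, or after 1 in 3 followed by 0 in the next 3 (Section 5.13); a 28-day window; at most 1 DLT in 6 at the MTD (Section 5.12).

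**Assumptions.** True DLT risk p over 28 days, with q = 1 − p; constant DLT hazard over the window; early-loss rate L of 3-7%. The upper end of L is the 28-day death risk under exponential survival with a 9-month median: 1 − 0.5^(28/274) = 6.8%. The 9 months come from Section 2.3, where they describe phase II studies of intravenous carboplatin ("Median progression-free and overall survival was approximately 3 and 9 months, respectively"). They are not a planning value for this trial.

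**All patients fully observed.** P(clear) = q³ + 3pq²·q³.
- p = 0.33: 0.3008 + 0.1337 = 0.434.
- p = 0.40: 0.309.

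**One of the first three leaves on day d.** That patient's chance of a DLT being seen is r = 1 − q^(d/28). Then P(clear) = q²(1 − r) + [2pq(1 − r) + q²r]·q³.
- p = 0.33, d = 7: r = 1 − 0.67^0.25 = 0.095. P = 0.4489 × 0.9047 + (0.4422 × 0.9047 + 0.4489 × 0.0953) × 0.3008 = 0.406 + 0.133 = 0.539.
- p = 0.33, upper bound r = 0 (no DLT would have appeared before departure): 0.4489 + 0.4422 × 0.3008 = 0.582.
- p = 0.40: 0.417 for d = 7, and 0.464 for r = 0.
- p = 0.10, d = 7: 0.932, against 0.906 fully observed.

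**The MTD rule, at most 1 DLT in 6, at p = 0.33.** Six observed: q⁶ + 6pq⁵ = 0.358. One of the six unobserved and counted without DLT: q⁵ + 5pq⁴ = 0.468.

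**Averaged over the early-loss rate.** Let each patient leave early with probability L, at a time uniform over the 28 days. The mean chance of a DLT being seen in a leaver is 0.176 at p = 0.33, so the effective risk is 0.33(1 − L) + 0.176L.

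| True risk | Fully observed | L = 3% | L = 7% |
| --- | --- | --- | --- |
| 33% | 43.4% | 44.3% | 45.6% |
| 40% | 30.9% | 31.8% | 33.1% |
| 10% | 90.6% | 90.9% | 91.2% |

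**Patients affected.** With no DLT at any level the trial treats 9 × 3 + 3 = 30 patients. At 3-7% this is 30 × 0.03 = 0.9 to 30 × 0.07 = 2.1, or about 1-2 patients.

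**The case against.** The strongest reply is that this turns silence into a rule. Section 9 makes receipt of drug necessary for the analysis, but does not call it sufficient. It says untreated patients are replaced, but does not say that nobody else may be. A DLT window of at least 28 days can be read as implying that each patient is observed for it, and Section 5.2 does say the first patient is watched for 28 days. This stands in part: a reader might infer that the protocol declares early leavers free of DLT, and no sentence does so. Still, the only replacement ground written is non-receipt of treatment, the counts are of patients entered or treated, and no section offers another rule. A team following the text would count the patient.

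The second reply concerns size. The rise from 43% to 54% or 58% applies only once a leaver has occurred. A level with 33% risk holds 3 to 6 patients, so about 0.1 to 0.4 leavers are expected there (3 × 0.03 to 6 × 0.07). The 1-2 leavers in 30 belong to the path without DLTs, where true risks are low and the effect is small. All of this stands.

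The third reply is that safeguards exist. Patients stay in hospital for the infusion and 12-24 hours beyond (Section 5.7). Adverse events are monitored on days 7, 14 and 28 (Section 7). A possible relation to the drug is enough for a DLT, and Section 8.1 extends attribution to the protocol, so a Grade 3 or 4 decline before an early death may already count. Entry requires a life expectancy of at least 3 months (Section 4.2), so the assumed 7% is probably high. These make the event rarer. They do not say how to count the patient when it happens.

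**Conclusion.** The point holds as a gap in the counting rule, of modest severity. As written, Section 9 with Sections 5.12 and 5.13 leaves a fully infused early leaver without a recorded DLT unreplaced and among the 3 or 6. That follows from the rules and is not stated in them.

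The direction is clear within a limit: counting such a patient as without DLT can only favour escalation and a higher MTD, but a patient whose DLT was seen before departure causes no such shift. The claim that the rule always biases the MTD upward is therefore too strong.

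At a true DLT risk of 33%, one day-7 leaver among the first three adds about 11 points to the chance of clearing the level (15 at most). Over an assumed 3-7% early-loss rate the expected shift is about 1-2 points. A reader might take the larger figure as the trial's expected bias; the documents do not support that, since they give no early-loss rate and the larger figure is conditional on a loss. All sizes rest on a constant DLT hazard and, for the average, on uniform leaving times.

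This need not wait for a statistical analysis plan: the rule decides in real time who enters the next level, and the protocol itself sets it.

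**What to change.** Add to Sections 9 and 5.13, in substance:

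- A patient is evaluable for DLT if a DLT occurred, or if the 28-day window was completed, including the Day 28 assessment.
- An infused patient who leaves observation earlier without a DLT, for a reason unrelated to study treatment, stays in the safety summaries, is not counted in the 3 or 6 for the escalation or MTD decision, and is replaced at the same dose level.
- State whether such replacements count toward the maximum of 42.

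The limit to unrelated reasons matters: replacing someone who left because of the treatment would remove information about toxicity. The reason for departure should therefore be documented before the escalation decision.

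The cost is a few sentences in an amendment and, on the assumptions above, perhaps 1-2 replacement patients over the trial. The Day 28 visit is already in the study calendar, and no dose or treatment rule changes.

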# 11 - Appendices

## Appendix A- Mini-Mental State Examination (MMSE)
